## Abstract

**Introduction:**

Environmental enteropathy (EE) is a syndrome affecting the gut characterised by villus blunting, reduced nutrient absorption and microbial translocation in children and adults experiencing a high burden of enteric infection due to inadequate access to clean water and sanitation.

**Methods and analysis:**

We will conduct coordinated randomised controlled trials in six countries to determine if supplementation with indispensable amino acids (IAAs) can improve intestinal barrier dysfunction in six geographically diverse populations of 18–36 months old children with stunting or severe stunting. All trials will measure the same primary outcomes while secondary outcomes will be measured on a per-trial basis using standardised protocols across the project. The primary endpoint will be change in gut permeability as assessed by the lactulose/rhamnose ratio. Secondary endpoints include changes in amino acid and carbohydrate absorption using novel, isotope tracer tests. Other prespecified outcome measures include changes in EE biomarkers and child weight. IAA supplementation will be given daily for 28 days and evaluation of the major endpoints will be at baseline and after 28 days of supplementation.

**Ethics and dissemination:**

Ethical approval will be obtained from the Research Ethics Committee at each participating site. Caregivers will provide written informed consent for each participant. Findings will be disseminated through peer-reviewed journals, conference presentations and face-to-face meetings with participant caregivers.

**Trial registration number:**

CTRI: CTRI/2024/06/069187 (India); ClinicalTrials.gov (NCT06617130, Malawi; NCT06676215, Philippines and NCT07256028, Morocco); Ongoing (Zambia); Ongoing (Morocco); PACTR: (PACTR202311714091884, Ghana).

STRENGTHS AND LIMITATIONS OF THIS STUDYOur study aims to better understand whether amino acid supplementation can promote gut health among stunted children, a question of global public health importance.Our coordinated study approach will enrol children from diverse low- and middle-income country settings.We use stable isotope-based tests to directly assess protein digestibility (using the dual stable isotope test) and carbohydrate absorption (using the ^13^C sucrose breath test).We are limited in our inability to examine long-term outcomes, such as improvements in linear growth associated with the intervention.

## Introduction

 Approximately 20% of children under 5 years worldwide experience chronic growth faltering,^1^ with lifelong consequences for health and well-being.^2^ While the causes of growth faltering are understood to be multifactorial,^3^ environmental enteropathy (EE), a condition defined by alterations in small intestinal structure and function,^4^ is an important risk factor for growth faltering in infancy.^5^,^7^

EE results from frequent exposure to enteric pathogens, especially in the context of inadequate or marginally adequate dietary protein intake^8^,^10^ and leads to increased intestinal inflammation, alterations to the gut microbiota and reductions in nutrient absorptive capacity in the small intestine.^11^ EE may also increase requirements for nutrients related to intestinal immune responses and recovery, especially high-quality dietary protein.^11^ Given that protein is required to provide indispensable amino acids (IAAs) for protein biosynthesis and normal growth in children,^12^ it has been hypothesised that the growth faltering observed in EE may result from depleted IAA status.^13^ There is some evidence to support this hypothesis from animal studies^13^; and lower circulating plasma concentration of some amino acids (eg, plasma citrulline and tryptophan) have been associated both with biomarkers of EE (urinary lactulose/rhamnose (LR) ratio)^14^ and linear growth faltering in children^15^ (figure 1).

**Figure 1 F1:**
[figure not shown]
Hypothesised relationships between EE, AA requirements and linear growth faltering. Hypothesised relationships related to how EE may impact AA requirements for children at risk of growth faltering. AA, amino acid; EE, environmental enteropathy.

Improving amino acid status may also promote recovery from EE, because amino acids have important benefits for gut health.^11^ Amino acids are both metabolised in enterocytes to support their high energy demands and used as building blocks for bioactive compounds required for immune response, epithelial renewal and mucin production.^16^ As a result, it has been proposed that nutritional interventions to prevent or optimise recovery from EE should provide IAAs to ‘replenish depleted stores’^11^ and improve gut health. Several studies have examined the impact of amino acid supplementation on EE biomarkers, primarily in adults, although with considerable variation in the amino acid supplement mix and with varying results.^17 18^ While most of these studies used the dual-sugar test (urinary lactulose/mannitol (LM) or LR ratio) as an outcome, one study in Zambian adults examined the gut directly and observed that tryptophan, leucine and glutamate supplementation protected against seasonal villus height reduction.^17^

An additional difficulty in EE research is that, although EE is hypothesised to impact the gut through functional changes to nutrient absorption, in many cases only limited measures of gut status (eg, inflammatory biomarkers) are assessed. The LM or LR ratio is a commonly used functional test for EE, but poses challenges in both administration and interpretation.^19^ To overcome this obstacle, stable isotope tracer tests have been developed to measure carbohydrate^20^ and protein digestion and absorption.^21^ The ^13^C sucrose breath test (^13^C-SBT) assesses intestinal sucrase-isomaltase activity, which may be suppressed in EED.^22^ The dual stable isotope test (DSIT) measures the digestion and absorption of protein-derived amino acids, making it especially valuable for understanding protein metabolism in children with EE or stunting. One study of Indian children using the DSIT found no statistically significant association between EE and amino acid absorption.^23^ Another study conducted in Pakistan hypothesised that children with EE may have compensatory/adaptive upregulation of enzymes associated with protein transport in the gut,^24^ which may help to explain these findings.

In this protocol, we describe a coordinated research project that aims to evaluate the impact of 28 days of IAA supplementation on EE among children with growth faltering in six low-resource settings.

### Hypothesis

IAA supplementation will improve biomarkers of gut function and functional measures of carbohydrate and protein absorption among children with stunting and at high risk of EE.

### Study objectives

The objectives of this study are to determine the effects of IAA supplementation for 28 days on:

The dual sugar LR ratio test.Secondary outcomes, including (1) other biomarkers of EE (plasma intestinal fatty acid binding protein (iFABP), plasma lipopolysaccharide binding protein (LPSBP), faecal myeloperoxidase (MPO) and faecal neopterin (NEO), (2) amino acid digestion, assessed by a DSIT, (3) carbohydrate digestion assessed by ^13^C-SBT and (4) weight gain.

## Methods and analysis

### Overview of the trial design

We will conduct a group of six coordinated, randomised controlled trials (RCTs). We opted for coordinated trials instead of a single, multisite trial to adhere to local regulatory and administrative guidelines and accommodate the logistical capacities and epidemiological context of each site. Each site will adhere to a core protocol, with variation in recruitment procedures (eg, recruitment through community, daycare or well-child visits) and room for additional outcome measures according to each site’s capacity (see online supplement 1 for full methodological details for each site). These trials will be conducted within the context of a larger, coordinated research programme that also includes complementary animal studies in France. In this protocol paper, we describe only the coordinated RCTs (figure 2) in six countries namely, Ghana, India, Malawi, Morocco, the Philippines and Zambia.

**Figure 2 F2:**
[figure not shown]
Coordinated research project design. A visual depiction of our coordinated research project design. AA, amino acid; 13C-SBT, 13C sucrose breath test; DSIT, dual stable isotope test; EE, environmental enteropathy; Gly-Sar, glycylsarcosine; iFABP, intestinal fatty acid binding protein; LPSBP, lipopolysaccharide binding protein; LR, lactulose/rhamnose test; MPO, faecal myeloperoxidase; NEO, faecal neopterin.

This is an open label study. In each trial, 18–36 months old children in the intervention arm will receive IAA supplementation for 28 days, while children in the control arm will receive only standard complementary foods for the same duration (figure 3). The study will be unblinded. Each of the six study sites will aim to recruit 60 children, half in the intervention arm and half in the control arm (see ‘Sample Size section’ for further details). Data collection began in August 2025 and is anticipated to be completed in all sites by June 2026. Site-specific start dates and enrolment status are reported in online supplement 1 (Standard Protocol Items: Recommendations for Interventional Trials (SPIRIT) guidelines for each site).

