### Laboratory analysis

Laboratory analyses will be conducted either on site or at centralised laboratories, depending on the requirements of the test outcome measure. Faecal biomarkers and plasma iFABP and LPSBP will be assessed on site. Urine samples will be sent to St John’s Research Institute laboratory for L/R analysis by gas chromatography mass spectrometry (MS). Plasma samples and test meal food samples will also be sent to St John’s Research Institute or the University of Glasgow laboratory for the ^2^H/^13^C DSIT analysis by liquid chromatography MS/MS. Breath samples will be sent to St John’s Research Institute laboratory for ^13^C analysis by isotope ratio mass spectrometry (IRMS) or to the University of Glasgow. Urine (total volume to be recorded) and plasma samples from children receiving an additional dose of ^15^N spirulina will be sent to AgroParisTech to be measured by EA-IRMS.

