#### Data collection, management and storage

Data collection tools include survey instruments and results of the outcome tests described above. All participant data will be collected using ID codes to maintain confidentiality and enable the participant’s tracking throughout the study period. All laboratory specimens will also be labelled with sample ID codes.

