#### Statistical analysis

To assess the effect of amino acid supplementation on markers of gut function in stunted children, we will first calculate summary values for the LR, ^13^C-SBT and the DSIT. Each of these tests may be summarised in various ways, and so our primary and secondary summary measures for each test are determined a priori. The LR test is the urinary excretion ratio (% of lactulose dose excreted/% of rhamnose dose excreted) over the test period; % lactulose excretion and % rhamnose excretion will be included as secondary outcomes. For the ^13^C-SBT, increases in atom per cent excess over baseline abundance will be converted to percentage of dose recovered (PDR) and curves are fit to the series of breath samples from each participant breath. From these breath curves, the time at which 50% of the final test dose is recovered (T_50_) will be considered as a primary outcome of interest. This choice is based on prior work that demonstrates that T_peak_ and T_50_ are associated with intestinal sucrase activity compared with other aspects of sucrose metabolism (eg, the fraction of the plasma bicarbonate excreted on the breath as opposed to excreted in urine or sequestered).^36^ Other summary measures of the ^13^C-SBT such as cumulative PDR by 90 min may also be influenced by misspecifications of CO_2_ production rate (VCO_2_), which is based on the participant’s estimated body surface area and sex.^52^ The DSIT is summarised as the % digestibility of specific amino acids from spirulina. The method of estimation is summarised in Devi *et al*.^21^ Weight-for-age Z-scores will be calculated based on WHO reference standards.^53^ Plasma concentrations LPSBP and iFABP and faecal concentrations of MPO and NEO will also be analysed.

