For all statistical analysis, p values <0.05 will be considered statistically significant and intention-to-treat analyses will be applied. Both our primary and secondary outcomes will be analysed as change from baseline to endline. Because LR ratios are generally not normally distributed, we will use the non-parametric Wilcoxon rank-sum test to compare the supplementation and control groups within each site. For combined analyses we will use logistic regression models (outcome: LR ratio above vs below EE cut-off, exposure: intervention or control group). For all secondary outcomes, we will similarly use the non-parametric Wilcoxon rank-sum test to compare the supplementation and control groups within each site. For combined analyses we will use linear regression models or logistic regression models based on appropriate cut-off values, including a random effect to account for clustering by site.

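### The study is declared unblinded for every role, but the lack of a placebo explains this only for caregivers and field staff; on-site assays, breath-curve fitting and open analysis choices could be masked cheaply

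*Protocol article*

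**What the plan says.** Under Overview of the trial design, in the paragraph after the Figure 2 caption, the article describes the blinding twice: "This is an open label study" and "The study will be unblinded". Neither sentence excepts a role, and no other section shown masks one. The same paragraph gives the reason for open delivery: "children in the control arm will receive only standard complementary foods for the same duration".

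Four other places bear on who could be affected by knowing the arm:

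- Laboratory analysis: "Faecal biomarkers and plasma iFABP and LPSBP will be assessed on site". The primary test goes elsewhere: "Urine samples will be sent to St John’s Research Institute laboratory for L/R analysis by gas chromatography mass spectrometry (MS". DSIT and breath samples are also sent to designated laboratories.
- Statistical analysis, on the breath test: "curves are fit to the series of breath samples from each participant breath". T50 is then taken from these curves.
- Statistical analysis, on combined analyses of secondary outcomes: "linear regression models or logistic regression models based on appropriate cut-off values".
- Data collection, management and storage: "All laboratory specimens will also be labelled with sample ID codes". For participant data, the stated purposes of the codes are confidentiality and tracking. Hiding the arm is not among them.

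**The concern.** Without a placebo, the people who deliver and observe the supplement cannot be masked, and nobody should ask for that. Assay, curve fitting and analysis are different. They come later, they use coded material, and they can be done without the arm. The blanket statement gives up masking there too, and gives no reason.

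At stake is arm-related judgement at steps where judgement is possible: repeating or rejecting an assay run, handling an odd breath sample or a poor curve fit, excluding a test, choosing a cut-off, and choosing between a linear and a logistic model. If the person deciding knows the arm, the decision can lean towards a result, even unintentionally. A later reader of an open-label trial cannot tell whether it did.

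**Working it through.** The plan states no figure on this point, so there is none to reproduce. The check sets each step against the reason for being open, and then gives one illustration of scale.

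**1. Does the unsupplemented control explain an open role?**

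| Role or step | Must know the arm? | Room for judgement, from the text |
|---|---|---|
| Caregivers; staff observing feedings (Intervention monitoring) | Yes | Not at issue |
| LR assay, central laboratory | No | Little: mass spectrometry on coded urine |
| DSIT and breath isotope assays, designated laboratories | No | Little: mass spectrometry |
| MPO, NEO, iFABP and LPSBP, assayed on site | No | Some: done at the sites that run the intervention |
| Breath-curve fitting | No | Some: fitted child by child, no curve form named in the article |
| Combined analyses | No | Some: model type open for secondary outcomes; cut-off values not given in the article, including the EE cut-off for LR |

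Only the first row is explained by the design. The last three rows carry the exposure.

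**2. Do other safeguards close the gap?** Opaque sealed envelopes (Randomisation) conceal the allocation before assignment and mask nothing afterwards. Specimen codes make masking feasible, but are not said to hide the arm. The summary measures are fixed in advance, with T50 named for the breath test. That narrows the choices but does not settle the curve form, the cut-offs or the model type.

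**3. Worst-case illustration for a secondary outcome.**

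Inputs: 60 children per site, half per arm, so 30 per arm per site (Overview). Table 2 plans the on-site biomarkers at six sites: 6 × 30 = 180 per arm. It plans the breath test at five: 5 × 30 = 150 per arm.

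Assumptions, not from the documents: normal outcome, no treatment effect, no site clustering, no missing data. The analyst sees the arms and reports the smallest p value out of four: a t-test and comparisons of proportions above the 25th, 50th and 75th percentiles.

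Results from 20,000 simulated trials per setting:

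| Per arm | Best of four, cut-offs at sample percentiles | Best of four, fixed cut-offs |
|---|---|---|
| 180 | 11.7% | 13.8% |
| 150 | 14.8% | 14.4% |

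The t-test alone rejects in about 5%. The difference between 180 and 150 per arm in the first column comes mostly from the discreteness of the counts and is not a sample-size effect. The usable reading is about 12% to 15%: 12/5 = 2.4 to 15/5 = 3 times the nominal rate.

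This is what choosing among analyses with the arms in view could do at worst. It is neither a measure of the effect of unblinding nor a prediction of how this team will work.

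**The case against.** The strongest reply is that the sentence is a design label in an overview. It does not say that laboratories or statisticians receive the allocation. Site methods are in online supplement 1, laboratory procedures in SOPs, and an analysis plan may exist; none is shown, and any of them might mask some roles. This stands as a limit on what can be claimed about conduct. It does not rescue the sentence: the article is not silent on blinding but declares a status for the whole study, and if another document masks some roles, the two must be reconciled.

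Three stronger readings are tempting and are not supported.

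- **The primary result is compromised.** A reader might infer this, but the LR assay is central, instrument-based and done on coded urine, and the combined primary model is already set as logistic. What remains for LR is the value of the cut-off, which an unseen analysis plan may give. Nor does the text support setting an assumed reading shift against the 0.40 SD target in Sample size. The documents give no such shift, and that target is set for ΔLR and DSIT, not for the on-site biomarkers.
- **Masking is the only protection, or the simulation shows what its absence costs.** The plan also has coded specimens, central measurement of key outcomes, summary measures fixed in advance and intention-to-treat analysis. The simulated inflation comes from open cut-offs and model type, and full prespecification would remove it with or without masking.
- **Masking is free.** The documents give no cost. Envelopes are opened at the sites, so bench staff there must be kept from the allocation, and whether every site can separate bench from field work is not stated. Equally, nothing says that bench staff do hold the allocation.

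**Conclusion.** The concern holds as a design choice that is broader than its justification. The lack of a placebo supports open caregivers and field staff. It does not support open assay staff, curve fitters or a statistician who knows the arms while choices are still open. The exposure lies mainly in MPO, NEO, iFABP and LPSBP assayed on site, in the breath-curve fits behind T50, and in the cut-off and model choices in the combined analyses.

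The size of any bias cannot be derived from the documents. The figure of about 12% to 15% in place of 5% is a worst case for secondary outcomes under the assumptions listed. No flaw in the primary LR assay is shown. The point is a worthwhile, inexpensive improvement. It rests on the article's statement applying as written, with no unseen document excepting these roles.

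**What to change.** In Overview of the trial design, replace the sentence declaring the study unblinded with wording such as:

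*Caregivers and field staff are not masked. Laboratory staff (on site and central), those fitting breath curves and the statistician work on ID-coded data without the arm until exclusions, cut-offs and models are locked. The allocation key is held by a person not involved in assay or analysis.*

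Apply it to every sample not yet assayed and to all analyses. Naming a keyholder outside assay and analysis matters: the coordinating team generates the sequence, and the article does not say whether the statistician belongs to that team.

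The cost is small. Specimens already carry codes, and neither the sample size nor any procedure for the children changes. Each site must keep opened envelopes away from bench staff. Data collection began in August 2025, so some samples may already have been assayed; those cannot be masked retrospectively, and the report should say which they are. Sample collection and caregiver report stay open under this design, and the fix does not reach them.

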**Figure 3 F3:**
[figure not shown]
Study flow chart. This figure shows the complete list of primary (LR) and secondary (DSIT, 13C-SBT, AAT, MPO, LPSBP and iFABP) biomarkers planned across the trials. Not all trials will administer all outcome measures. AA, amino acid; AAT, alpha-1 antitrypsin; 13C-SBT, 13C sucrose breath test; DSIT, dual stable isotope test; iFABP, intestinal fatty acid binding protein; LAZ, length-for-age z-score; LPSBP, lipopolysaccharide binding protein; LR, lactulose/rhamnose; mo, month old; MPO, faecal myeloperoxidase.

### Data collection and participant timeline

The overall timeline for each participant in the studies is visualised in figure 4. Each study site will follow their own preferred protocol for recruitment and enrolment. Following enrolment, baseline study procedures will be completed over two visits. Each participating child will then be provided with amino acid supplementation at the daily dosage described in table 1, for 28 days. End-line data will again be collected over two visits, with flexibility for scheduling based on the outcome measures each site intends to collect and logistical preferences (table 2). Each site will manage data entry, data storage and other data management procedures in accordance with local regulations and institutional guidance. A detailed description of the study intervention and aspects of the specific outcome tests and measurements to be performed at baseline and endline are described in figure 4 and further detailed below:

### Ethics declaration

**Figure 4 F4:**
[figure not shown]
Protocol timeline. This figure shows the complete list of primary (LR) and secondary (DSIT, 13C-SBT, AAT, MPO, LPSBP and iFABP) biomarkers planned across the trials. Not all trials will administer all outcome measures. AAT, alpha-1 antitrypsin; 13C-SBT, 13C sucrose breath test; DSIT, dual stable isotope test; iFABP, intestinal fatty acid binding protein; LPSBP, lipopolysaccharide binding protein; LR, lactulose/rhamnose; MPO, faecal myeloperoxidase.

**Table 1 T1:** A representative total dose of the IAA supplement in milligrams per day, calculated for a 24-month-old child

IAA	Dose
Gly	232.1 mg/day
His	252 mg/day
Ile	453.6 mg/day
Leu	907.2 mg/day
Lys	739.2 mg/day
Met	246.3 mg/day
Cys	123.1 mg/day
Phe	336.0 mg/day
Tyr	336.0 mg/day
Thr	403.2 mg/day
Trp	100.8 mg/day
Val	604.8 mg/day
Total	4734.5 mg/day

Gly is added to support intestinal glutathione synthesis.^54^ The Gly dose is calculated as 63% of AA intake using whole egg protein as a reference.

AA, amino acid; Cys, cysteine; Gly, glycine; His, histidine; IAA, indispensable amino acid; Ile, isoleucine; Leu, leucine; Lys, lysine; Met, methionine; Phe, phenylalanine; Thr, threonine; Trp, tryptophan; Tyr, tyrosine; Val, valine.

**Table 2 T2:** Planned outcome measures in each site

	Ghana	India	Malawi	Morocco	Philippines	Zambia
LR	5-hour	5-hour	5-hour	3-hour	5-hour	3-hour
DSIT	Yes	Yes	Yes	Yes	Yes	No
13C-SBT	Yes	Yes	Yes	Yes	Yes	No
Faecal MPO and NEO	Yes	Yes	Yes	Yes	Yes	Yes
LPSBP and iFABP	Yes	Yes	Yes	Yes	Yes	Yes

13C-SBT, 13C sucrose breath test; DSIT, dual stable isotope test; iFABP, intestinal fatty acid binding protein; LPSBP, lipopolysaccharide binding protein; LR, lactulose/rhamnose; MPO, myeloperoxidase; NEO, neopterin.

Ethical approval for the study has been obtained from the Ethical Review Board overseeing research at each site. The research protocol follows ‘the Standard Protocol Items: Recommendations for Interventional Trials (SPIRIT)’.^25^

